## Data analysis

## Plan for Analysis

**Research question 1.** What is the feasibility of implementing the OASIS Walking Intervention in community-dwelling older adults with cognitive impairment in facility-based transitional care programs, as determined by recruitment rate, retention rate, and adherence?

Data will be analyzed using SPSS version 28.0.1.0. Descriptive statistics will be used for the demographic variables as well as for measures of feasibility (recruitment rate, retention rate, and adherence).

**Research question 2.** What is the satisfaction of older adults with CI with the OASIS Walking Intervention?

Satisfaction will be also assessed through the opened ended questions in the CSQ satisfaction surveys. Data will be analyzed using descriptive statistics. The qualitative data from the open-ended questions as well as field notes from the interventionist will be analyzed using content analysis (58).

**Research question 3.** Does the OASIS Walking intervention result in improved muscle strength, mobility, functional status, and quality of life in older adults with cognitive impairment?

Means and standard deviations for each of the outcome measures will be summarized. Longitudinal plots of overlaid individual trajectories will be used to visualize observed change over time. To analyze question 2 regarding efficacy, repeated measures analysis of variance (ANOVA) (59, 60) will be used to determine if the intervention results in an improvement in participants’ time to perform one sit to stand, 2MWT, BI, and quality of life over time. Repeated measures ANOVA is a parametric test that determines if the means of three or more measures from the same person are similar or different (60).

In order to use the test, the interventionist will check if the assumptions are met: 1) the participants are not related to one another; 2) there are at least three measures of the dependent variable; 3) there is a good range of values; 4) the dependent variable is not clearly skewed; and 5) the dependent variable is of a ratio measurement scale (60). If at least one of the assumptions is not met, the Friedman’s ANOVA by rank, a non-parametric test that is analogous to the single factor repeated-measures ANOVA (60), will be used instead. If all assumptions are met and if a significant *f* test results from the repeated measures ANOVA, the modified Bonferroni test (a more conservative test that is good to use with a smaller number of comparisons), will be used to determine which means are significantly different from each other (60). Scatter plots will be used to demonstrate any changes in outcomes. If there is missing data, paired t-tests will be used to determine if there is an improvement in participants’ time to perform one sit to stand, 2MWT, BI, and quality of life between two time points.

**Research question 4.** What percentage of the participants were discharged home and how many were discharged to the nursing home post intervention? Percentages will be used to describe discharge destination of participants.

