**Secondary Outcomes**

Efficacy will be assessed using measures for muscle strength, mobility, functional status, quality of life, and discharge destination. The primary outcome for efficacy will be lower extremity **muscle strength**.

**1. Lower extremity muscle strength.** Lower extremity muscle strength will be measured using the time to perform one sit-to-stand (42, 43). Time to perform one sit-to-stand has good validity and reliability. The ability to perform one sit to stand has been used in a study involving sit-to-stand activity with older adults with dementia in nursing homes (31). Repeated observations of the sit to stand test by one observer yielded correlations of 0.89 to 0.96 (44).

Older adults who are frail, such as those who are in nursing homes, must use their arms to stand and may be unable to complete more than one sit to stand (45). For a study involving sit-to-stand activity with older adults with dementia in nursing homes, participants were asked to stand from a seated position three times, with the time to complete the sit to stand measured at the third time using a stopwatch (31, 45) (personal communication with [name] January 16, 2023). Similarly, for the present study, the interventionist or RA will ask participants to stand from a seated position three times, with the time to complete the sit to stand measured at the third time using a stopwatch (Appendix E). The interventionist and the RAs will measure the time to complete the sit to stand for participants until ≥75% interrater agreement is reached (46). Then only one RA or the interventionist will collect the rest of the outcome measures data.

**2. Mobility.** Mobility will be measured using the two-minute walk test (2MWT). The 2MWT has good validity and reliability. It has been used in studies involving older adults with dementia in nursing homes (23, 34). As well, the 2MWT has been shown to provide sufficient data to objectively quantify gait measurements, similar to the six-minute walk test (47). The 2MWT has a test-retest reliability coefficient of 0.98 (0.96–0.99) and an inter-rater reliability of 0.92 (0.86–0.96) when assessed in frail older adults with dementia (34). Distances walked for the 2MWT among older adults with dementia in nursing homes and day care centers ranged between 63.1-63.6 meters (34). The minimal detectable change (MDC), that is, the minimum change that is considered a true change in performance, for the 2MWT is 9.1 meters (34).

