# STATISTICS

**Sample Size**

An activity-based study involving older adults with dementia in the nursing home setting (31) that used time to perform one sit to stand found a moderate effect size (Cohen’s d) of 0.48. Since the present study will use repeated measures ANOVA, a Cohen’s *f* of 0.25 (a suggested value for moderate effect size) (55) was used in the sample size calculation. Based on an *f* of 0.25, a power of 0.8 and an alpha of 0.1, in keeping with those used in a mobility study involving older adults with dementia (23), a sample of 21 participants will be needed for this study. Using an alpha of 0.1 can be acceptable for exploratory or preliminary studies (56) (p. 188). An attrition rate of just under 20% over the course of a 6-week study will be taken into account, as was experienced in a 6-week intervention study involving older adult residents with dementia (28). Thus, a sample of 26 participants will be recruited for this study. G*Power 3.1.9.7 software (57) was used for the sample size calculation for an ANOVA: Repeated measures, within factors statistical test with one group, three measurements, 0.6 for the correlation among repeated measures, and 0.8 for nonsphericity correction (which is a mild departure from sphericity) (56).

The sample size is achievable based on input provided by our collaborating TCP administrators, as the TCP has a 35-bed capacity and most patients have cognitive impairment.

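### The skewness check that replaces the repeated measures ANOVA with Friedman's test looks at raw outcome values, although the sized F-test depends only on within-person deviations

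*Protocol*

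**What the plan says.** Under Sample Size, the Protocol sizes the study on "ANOVA: Repeated measures, within factors statistical test with one group", with an f "of 0.25 (a suggested value for moderate effect size"), "a power of 0.8 and an alpha of 0.1", and "three measurements, 0.6 for the correlation among repeated measures, and 0.8 for nonsphericity correction". This gives 21 evaluable participants, raised to 26 for attrition of just under 20%.

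Under Plan for Analysis (research question 3), "the interventionist will check if the assumptions are met: 1) the participants are not related to one another". Check 2 is at least three measures. The next two are "3) there is a good range of values; 4) the dependent variable is not clearly skewed". Check 5 is a ratio scale. One failed check is enough for Friedman's test to be used in place of the ANOVA. Pairwise comparisons are described only for the other branch: "If all assumptions are met and if a significant" F-test results.

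Time to perform one sit-to-stand is named under Secondary Outcomes as the primary efficacy outcome. It is on a ratio scale, so check 5 does not touch it and check 4 can decide its test. The same holds for the two-minute walk test. The Barthel Index and QOL-AD are summed scores, so check 5 sends them to Friedman whatever their skewness.

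**The concern.** The F-test for time in a one-group repeated measures ANOVA compares visit means against the person-by-visit residual. Each participant's own level drops out of both. A long right tail of slow participants therefore says nothing by itself about the validity of the test, yet check 4 treats it as disqualifying.

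Such a tail is plausible. The inclusion criteria admit people who walk independently and people who need one person's help, and the Protocol notes that frail older adults "must use their arms to stand and may be unable to complete more than one sit to stand". At stake is the power planned for the primary efficacy outcome: the sized test could be exchanged for one that the sample size calculation does not cover, for a reason that does not bear on its validity.

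Checks 1 and 2 are also illogical as triggers. Friedman's test needs unrelated participants just as the ANOVA does, and it does not supply a missing third measure.

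**Working it through.** **1. The plan's own figure.** Inputs from Sample Size: f = 0.25, alpha = 0.10, m = 3 measurements, rho = 0.6, epsilon = 0.8.

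- Noncentrality: lambda = n·m·f²·epsilon/(1 − rho) = 21 × 3 × 0.0625 × 0.8/0.4 = 7.875.
- Degrees of freedom: df1 = (m − 1)·epsilon = 1.6; df2 = (n − 1)(m − 1)·epsilon = 32.
- Power is 0.811 at n = 21 and 0.792 at n = 20, so 21 is exact.
- With 19% attrition, 21/0.81 = 25.9, so 26.

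Both stated figures reproduce.

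**2. Does F depend on person levels?** One set of within-person data was combined first with a symmetric person component and then with a strongly skewed one. Sample skewness at one visit moved from −0.10 to 2.40. F was 5.627 both times.

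**3. Cost of a needless switch.** Simulations used n = 21, alpha 0.10, a linear trend with f = 0.25, and Friedman with its chi-square reference. The distribution shapes are assumptions, because the Protocol gives no distribution for sit-to-stand time.

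| Setting | F on raw values | Friedman | F on log values |
|---|---|---|---|
| Log-normal person levels, normal within-person noise, epsilon 1 | 0.86 | 0.76 | – |
| Planned epsilon 0.8 (correlations 0.7, 0.7, 0.4) | 0.78 | 0.67 to 0.68 | – |
| Multiplicative times, log SD 0.5 to 1.0 | 0.79 down to 0.59 | 0.76 | about 0.86 |
| Log-normal within-person noise | 0.86 to 0.88 | 0.98 to 0.997 | – |

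In the first row the uncorrected F-test holds its level under the null (0.102 at nominal 0.10), so nothing is gained by leaving it. The loss is 0.86 − 0.76 = 0.10. At epsilon 0.8 it is also about 0.10.

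As a cross-check, the asymptotic efficiency of Friedman relative to F under normal errors is 3k/(π(k + 1)) = 9/(4π) = 0.716 for k = 3. On that measure 21 participants analysed by Friedman are worth about 21 × 0.716 = 15 analysed by F.

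**4. Cost of the rule as a whole.** The switch does not happen in every trial. In the first setting, baseline skewness exceeds 1 in about 30% of trials. Applying the Protocol's one-way rule with an assumed cut-off of absolute skewness above 1 at any visit gives power of 0.82 to 0.83 against 0.86 (a loss of 3 to 4 points). At epsilon 0.8 it gives 0.75 against 0.78 (3 points).

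**5. Error rate.** Under the null, the one-way rule rejects in about 10% to 12% of trials. A rate of about 15% arises only if both tests are run and the significant one is reported.

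**The case against.** The strongest reply is that raw skewness is often a fair proxy. For positive times, slower people usually also vary more, so a skewed outcome tends to come with skewed within-person deviations, and these do affect F. In that case Friedman is comparable or better: 0.76 against 0.72 for raw F at log SD 0.7, and 0.76 against 0.59 at log SD 1.0. This stands. The switch can gain power as well as lose it, and Friedman cannot be called the weaker test in general. It does not rescue the check, because raw values cannot tell the two cases apart while residuals can. In the multiplicative case the log scale does better than either planned test.

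A reader might infer several stronger things that the Protocol does not support:

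- **A false-positive rate of 15%.** The text gives one directional rule, not a choice of the better result, and that rule stays near 10%.
- **No size of change after Friedman.** Plan for Analysis promises means, standard deviations and individual trajectories without condition. The omnibus F is non-directional too. Pairwise follow-up after Friedman is unstated, not ruled out.
- **A judgement made by eye.** The text says only that the interventionist checks. A skewness statistic and cut-off may stand in a statistical analysis plan that is not shown.
- **A skewed sample as a fact.** The remark about arm use describes frail people such as nursing home residents. Entry here requires current ambulation with at most one person's help and physiotherapist clearance.

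Checks 1 and 2 are unlikely to change any analysis: three visits are fixed by design and nothing suggests related participants.

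**Conclusion.** The point holds as a misdirected rule. The Protocol fixes both the target of the check (the dependent variable) and its consequence (Friedman instead of ANOVA), and the target is wrong for the test that was sized. Where only person levels are skewed, a needless switch costs about 10 points of power, or about 3 to 4 points averaged over trials. Where within-person deviations are skewed as well, the switch costs little or helps, but ANOVA of log time would serve better for multiplicative times.

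These sizes rest on assumed log-normal shapes, a linear trend and an assumed cut-off of 1. That F does not depend on person levels needs none of these assumptions. Severity is minor: feasibility is the primary outcome, and efficacy is a secondary question in an uncontrolled study that adopts alpha 0.1 as exploratory.

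**What to change.** In Plan for Analysis, research question 3:

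1. Judge skewness on the model residuals or within-person changes, by a rule stated in advance, and not on raw values.
2. Name the repeated measures ANOVA with a sphericity correction as the main analysis of sit-to-stand time, on the log scale if the residuals are skewed, and show the mean change in seconds beside it.
3. Report Friedman's test as a sensitivity analysis.
4. Remove checks 1 and 2 as triggers for Friedman; keep them as conditions for either test.

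The change is to wording only and adds no participants, visits or measurements. The small downside is that a log analysis yields a percentage change, so the change in seconds has to be reported as well, not least because the Study Hypotheses set their threshold in seconds (0.87).

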## Stopping rules or discontinuation criteria

We will collect data on patients once they are admitted to the unit. Once they are discharged (including back to acute care, another site or back home) we will discontinue collecting data on the patient and we will keep track of their discharge disposition. If the patient after consenting decides to discontinue being in the study, we will withdraw them from the study.

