The testing procedure for the 2MWT to be used will be similar to the ones used in studies involving older adults with cognitive impairment in nursing homes (34, 48) (Appendix E).

**3. Functional status.** Functional status will be measured by the Barthel Index (BI) (Appendix E), which has been shown to have a good reliability (kappa > 0.75) and validity for short stay older adult patients (49) and has acceptable item reliability (1.0) and person reliability (0.88) in older adults with dementia (50). BI is a 10-item questionnaire which is scored out of 20, with higher scores meaning a better outcome. A change in BI score of 1 point is considered a meaningful change in a person’s level of independence (35). When the BI score is multiplied by 5, a score of 0-20 indicates total dependency, 21-60 indicates severe dependency, 61-90 indicates moderate dependency, and 91-99 indicates slight dependency (51). BI scores will be measured at pretest, time 2, and post-test.

**4. Quality of life.** Quality of life will be measured using the QOL-AD Quality of Life–Alzheimer’s Disease, a 13-item questionnaire that asks about physical health, energy, mood and other quality of life measures that can be answered by older adults with CI (52). The QOL-AD has good reliability (α from 0.83 to 0.90) and validity correlation with measures of depression (r = −0.41 to −0.65) (52). A study involving a walking program for older adults with CI in nursing homes resulted in significant improvements to self-reported QOL-AD (27). It takes about 10 minutes to complete the QOL-AD (53). The QOL-AD will be completed by the SDM if the patient is not able to complete it.

5. Satisfaction. Participant satisfaction will be determined using the Client Satisfaction Questionnaire (CSQ) (54), with the cover page for the questionnaire tailored to the TCP setting, which includes 8 Likert scale questions, a comments section; and three open ended questions as was used in the work by Sano and colleagues (33) (Appendix G). As well, qualitative data in the form of field notes will also be taken on interventionists’ report of challenges, issues, and ease of intervention delivery (41). Field notes taken within the intervention fidelity checklist (Appendix S) will also capture interventionists’ perspectives on elements of the intervention that are satisfactory to participants and their care partners. The CSQ will be completed by the SDM if the patient is not able to complete it.

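### The missing-data and ratio-scale fallback rules conflict with the repeated-measures ANOVA planned for all four efficacy outcomes, and leave the test, the time points and the error control undetermined

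*Protocol*

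**What the plan says.** Table 2 and the Plan for Analysis (research question 3) give one test for all four efficacy outcomes, repeated-measures ANOVA. The text states that this test "will be used to determine if the intervention results in an improvement in participants’ time to perform one sit to stand, 2MWT, BI, and quality" (the last item being the QOL-AD). The Sample Size section is built on the same test, with Cohen's f "of 0.25 (a suggested value for moderate effect size"), "a power of 0.8 and an alpha of 0.1", three measurements, correlation 0.6 and nonsphericity correction 0.8. It arrives at 21 participants, raised to 26 because "An attrition rate of just under 20% over the course of a 6-week study will be taken into account".

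The Plan for Analysis then adds three conditional rules:

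- **Scale and other assumptions.** Five conditions are listed, the last being that "the dependent variable is of a ratio measurement scale (60). If at least one of the assumptions is not met", Friedman's test replaces the ANOVA.
- **Post-hoc comparisons.** The modified Bonferroni test is used if all assumptions hold and the ANOVA F is significant.
- **Missing data.** "If there is missing data, paired t-tests will be used to determine if there is an improvement in" the four outcomes between two time points. No amount of missing data is specified, and the two time points are not named.

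Two other statements bear on these rules. On functional status, "BI is a 10-item questionnaire which is scored out of 20"; the QOL-AD is described as a 13-item questionnaire. Under the stopping rules, "Once they are discharged (including back to acute care, another site or back home) we will discontinue collecting data on the patient".

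**The concern.** An analysis plan should let a reader know, before any data exist, which test will be reported for each outcome. Here two of the four outcomes appear to fail the ANOVA's entry condition by the way they are scored. All four are also exposed to a missing-data rule whose trigger the plan itself expects to occur.

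Three things are at stake:

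- The choice of test, and of the pair of time points, could be made after the data are seen.
- The only multiplicity adjustment in the plan is attached to the ANOVA route.
- Any analysis that needs a T3 value leaves out people discharged before T3, and their course may differ from that of those who stay.

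**Working it through.** **1. The plan's own figure.** Using the G*Power within-factor form, with f = 0.25, m = 3, ρ = 0.6, ε = 0.8 and α = 0.10 (Sample Size):

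- λ = f²·N·m·ε/(1−ρ) = 0.0625 × 21 × 3 × 0.8/0.4 = 7.875
- df = (m−1)ε = 1.6 and (N−1)(m−1)ε = 32
- Power is 0.811 at N = 21 and 0.792 at N = 20, so 21 is the smallest adequate N.
- 21/(1−0.19) = 25.9, which rounds up to 26.

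Both stated figures reproduce. The sample size is sound for the test it names.

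**2. Which rule each outcome meets.**

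| Outcome | Table 2 and Sample Size | Ratio-scale rule | Missing-data rule |
| --- | --- | --- | --- |
| Sit-to-stand time | ANOVA | passes | paired t |
| 2MWT | ANOVA | passes | paired t |
| Barthel Index | ANOVA | Friedman | paired t |
| QOL-AD | ANOVA | Friedman | paired t |

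Time and distance are ratio measures. A sum of 10 or 13 questionnaire items is not. The protocol does not classify the scales, so that is an inference, but a standard one. The last two rows receive a rank test from one rule and a parametric test from the other, with no order of precedence.

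**3. How likely the missing-data condition is.** With independent loss at rate d, P(all 26 complete) = (1−d)^26.

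- d = 0.20: 0.3%
- d = 0.19: 0.4%
- d = 0.10: 6.5%
- d = 0.05: 26%

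At the planned attrition the condition is met with probability above 99%, and about 26 × 0.19 ≈ 5 people would lack T3.

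**4. Family-wise error if the paired t-tests are used.** Simulation under no change, n = 21, exchangeable correlation 0.6, each test two-sided at 0.10:

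- all three pairs: about 23–24% per outcome (independent tests would give 1−0.9³ = 27%)
- the two contrasts with T1: about 18%
- one pair named in advance: 10%

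The protocol does not say which case applies.

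**5. Power of a paired test.** A linear trend with f = 0.25 has means −x, 0, x with √(2x²/3) = 0.25, so x = 0.306 and the T1–T3 difference is 0.612 SD. The SD of the difference is √(2 × 0.4) = 0.894, giving a standardised change of 0.685. A two-sided paired t-test at α = 0.10 with n = 21 then has power of about 0.92, against 0.81 for the ANOVA. For a T1–T3 change of 0.48 SD the power is 0.77.

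**6. Effect of leaving out people without T3.** This is an illustration. The true T1–T3 change is set at 0.48 SD, with 20% dropout whose log-odds depend on the T1–T2 change. The protocol gives no strength for this dependence, so it is varied.

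- Weak (slope 0.25 per SD): completers average 0.46 if improvers leave and 0.50 if decliners leave. The error is 0.02/0.48, or about 5% before rounding.
- Strong (slope about 1 to 1.5 per SD): about 0.39 and 0.57. The error is 0.09/0.48, or about 19%.

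A likelihood-based model using every observed visit returns 0.48 in each case, because dropout here depends only on observed values. If dropout instead depends on the T1–T3 change itself (slope 1), that model gives 0.37 and 0.59, and completers give 0.33 and 0.63.

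**The case against.** The strongest reply is that the missing-data sentence does not say the t-tests replace the ANOVA. The Friedman sentence does use replacement wording; this one does not. Inflating 21 to 26 also suggests that the authors expected about 21 completers in an ANOVA, with t-tests as a supplement. That reading is plausible, so the documents do not establish that the ANOVA will be run on no outcome. They leave the matter open, and even on this reading the ratio-scale rule still removes the Barthel Index and QOL-AD.

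Other parts of the reply stand:

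- A reader might infer lost power. Step 5 shows none for a trend of the planned size.
- A reader might infer that Friedman leaves nothing to compare with the 1-point and 3-point criteria in the Study Hypotheses. The Plan for Analysis and Table 2 report means and SDs whichever test is run.
- A reader might call the paired tests completer-only. A T1–T2 test keeps those who leave after T2. Only pairs that include T3 drop them, as a listwise ANOVA also would.
- A reader might assume that discharge reflects recovery or decline. The stopping rules name home, acute care and another site as exits, but the protocol gives no reasons for the timing of discharge.

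One part does not stand. The Plan for Missing Data cites an earlier study with no missing data, but the Sample Size section plans for just under 20% attrition. The retention measures concern assent and remuneration, which do not prevent discharge.

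**Conclusion.** The point holds as a conflict between stated rules. The Barthel Index and QOL-AD are excluded from their assigned test by the plan's own scale condition. Read literally, the missing-data rule covers all four outcomes and is triggered with over 99% probability, assuming independent loss at the planned rate. The time points are unnamed, and for two outcomes the rules collide.

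The size depends on how the gap is filled. Family-wise error per outcome runs from 10% (one named pair) to about 23–24% (all three pairs). Bias in a T1–T3 completer mean is illustratively 5–20% of a 0.48 SD change if leaving tracks early change, and the protocol gives no basis for choosing a value in that range.

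This should be fixed but is not critical. Feasibility is the primary outcome and is analysed descriptively; efficacy is secondary in a single-arm study whose alpha of 0.10 is justified as exploratory.

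**What to change.** Delete the ratio-scale condition and the paired-t rule. Analyse all four outcomes with one linear mixed model (MIXED in SPSS, the software already named), with time as a three-level factor and an unstructured covariance, using all available T1, T2 and T3 data. Then:

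- name T1–T3 as the primary contrast, with a 90% confidence interval to match alpha 0.10;
- apply the modified Bonferroni to any other pairwise contrasts;
- keep Friedman and Wilcoxon as sensitivity analyses;
- state that the estimates are unbiased only if dropout depends on observed data, and report discharge reasons alongside the results.

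The timing of T3 should stay as it is, because Table 2 ties it to the end of the six-week intervention.

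The cost is slightly more analysis work and some rewording. The Sample Size section should add that its ANOVA calculation approximates the mixed-model test of time; 21 and 26 need not change.
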